## Methods

### Trial design

This clinical study is a parallel, two-armed, open label, non-inferiority randomised controlled trial with a 1:1 allocation ratio between the experimental intervention arm (pulpotomy) and the active comparator arm (pulpectomy).

### Trial setting

This clinical trial will be conducted in the Paediatric Dentistry Department of Christian Dental College Ludhiana, India.

### Trial registration and protocol

As mandated by the International Committee of Medical Journal Editors (ICMJE) and jurisdictional legislation for conducting clinical trials in India, this trial has been prospectively registered on ClinicalTrials.gov and the Central Trial Registry—India (CTRI). Ethics approval has been obtained from the Institutional Ethics Committee of Christian Medical College Ludhiana (IEC Approval Number: 23-12-517/CDC) This clinical trial protocol follows the SPIRIT guidelines (Standard Protocol Items: Recommendations for Interventional Trials). Any protocol changes required in the future will be carried out on the ClinicalTrials.gov.

### Study participants: eligibility criteria

Healthy (ASA I and II) co-operative children (Frankl Scale + and + +) between the ages of 4 to 9 years will be invited to participate in the study if they have vital primary molars that meet the following *inclusion criteria*: (i) symptoms typical of irreversible pulpitis i.e., spontaneous unprovoked pain lasting few seconds to several hours in the days before the dental visit or pain that is exacerbated by hot and/or cold stimuli with the pain lingering even after removal of stimuli; (ii) post-deroofing the pulp chamber, vitality of the primary molar tooth is confirmed by visual inspection of pulpal haemorrhage (uniformly reddish pink vascular tissue indicates healthy pulp); (iii) post-coronal pulp amputation, radicular pulp health is confirmed by attainment of radicular pulp haemostasis within 8-min of compression with a 5% sodium hypochlorite (NaOCl)-dampened cotton pellet; (iv) the primary molar is restorable with stainless steel crown; and iv) any physiologic root resorption, if present, is less than 1/3 the normal root length.

The *exclusion criteria* include: (i) clinical examination reveals signs of pulpal infection i.e., pathologic tooth mobility, parulis/fistula, or soft tissue swelling; (ii) pre-operative periapical radiograph suggests presence of furcal radiolucency more than ½ the furcation to periapical area; (iii) pre-operative periapical radiograph suggests presence of periapical radiolucency; (iv) pre-operative periapical radiograph suggests presence of pathological root resorption (v) post-deroofing the pulp chamber, visual examination of pulp tissue reveals signs of necrosis i.e., avascular/minimally bleeding pulp tissue or yellowish necrotic areas/purulent exudate; (vi) post-coronal pulp amputation, there are signs of extensive radicular pulp inflammation i.e., bleeding continues even after 8-min compression with NaOCl-soaked cotton pellet; and (vii) parents not willing to place full coverage crowns post-treatment; and (vii) if both primary molars in the quadrant are painful and clinical diagnosis of irreversible pulpitis between the teeth is not sharply defined.

### Trial interventions

The proposed trial interventions, pulpotomy and pulpectomy, will adhere to standard clinical procedural guidelines. Treatment group allocation of the consenting trial participants to one of the two intervention groups will be carried out only after intra-operative confirmation of pulp vitality and achievement of radicular pulp haemostasis. The choice of the treatment group (pulpotomy or pulpectomy) will be revealed to the operating clinician by an independent allocator only after coronal pulp amputation and confirmation of pulp vitality and haemostasis. Participants with pulp assessed to be non-vital or with uncontrolled bleeding from the pulp stumps will be excluded prior to allocation.

Standard clinical protocol for the pulpotomy group:Detailed history of symptoms will be verified and a thorough clinical examination shall be performed.Pre-operative pain intensity will be recorded using the validated five-face visual analogue scale (VAS) commonly used for pain intensity measurement in children (Fig. 1). After giving explanations of the VAS, children will be requested to select one of the faces that best reflect their pain intensity.A standard pre-operative periapical radiograph will be taken using a paralleling technique and a film holder device. Care will be taken to ensure that the radiographic image extends beyond the root tip of the primary molar tooth and there is no evidence of distortion, overlap, or processing errors.Local anaesthesia will be achieved with 2% lidocaine or 4% articaine containing 1:100,000 epinephrine and the tooth will be isolated under rubber dam.To minimize further bacterial contamination of the pulp, carious tissues will be progressively removed, starting at the periphery of the cavity and then over the pulp chamber roof.Once pulp chamber deroofing is complete, a fresh sterile bur will be used to remove all coronal pulp tissue to the level of the root canal orifices, under copious water irrigation. During this step, intra-operative assessment of pulp vitality will also be carried out. Healthy vital pulp will present as uniformly reddish pink vascular tissue, while non-vital necrotic pulp will present as dark avascular tissue with minimal bleeding or as yellowish liquefied areas. If pulp is judged to be necrotic, the tooth will be excluded from the study. Further treatment of such excluded teeth will be delivered following local management protocols.Haemostasis and disinfection of the radicular pulp tissue will be carried out by compressing a 5% NaOCl-soaked sterile cotton pellet over the pulp stumps for up to 8-min. Up to three attempts will be made to control pulp stump bleeding using moderate pressure applied with the NaOCl-dampened cotton pellet. Pulpal haemostasis will be assessed at three timepoints (3-, 6-, and 8-min) and the pulpotomy medicament placed over the pulp stumps as soon as haemostasis is achieved. If bleeding persists beyond 8-min, the radicular pulp shall be considered irreversibly inflamed, and the tooth will be excluded from the study. Further treatment of such excluded teeth will be delivered following local management protocols.Once haemostasis is achieved, 2 mm of a pre-mixed mineral trioxide aggregate (MTA) (NeoPutty, NuSmile, Houston, TX, U.S.A) medicament will be directly adapted over the pulp stumps ensuring that there is no porosity or any excess cement on the pulp chamber walls.The access cavity will be restored with a bulk-fill high-strength glass ionomer cement (3M ESPE Ketac Molar, Seefeld, Germany). Post-operative radiograph will be taken to confirm fidelity to the pulpotomy procedure.The pulpotomy-treated tooth will be prepared for receiving a full coverage stainless steel crown (SSC) one week after the pulpotomy procedure.

**Fig. 1 Fig1:**
[figure not shown]
Visual analogue scale for pain assessment in children

Standard clinical protocol for the pulpectomy group:

The initial seven procedural steps of the pulpotomy treatment group shall be followed in the pulpectomy treatment group too. Once vitality is confirmed and haemostasis achieved, the entire radicular pulp will be extirpated, and the root canals prepared as described below:Radicular pulp will be extirpated from all the root canals using appropriate endodontic instruments.Maintaining a working length 1–1.5 mm short of the radiographic apex, chemo-mechanical preparation of the canals will be done using a series of 21 mm long Kerr-type endodontic files up to file no. 30 or 35 (depending on the initial size of the canal). Regular irrigation of the prepared canals will be carried out using 2.5% NaOCl alternating with saline.Sterile absorbent paper points will be used to dry the root canals prior to obturation with root filling material that contains zinc oxide-eugenol, Ca(OH)_2_, and iodoform (Endoflas; Sanlor Laboratories, Cali, Colombia). The Endoflas material that is available in a powder-liquid form will be mixed into a medium consistency such that it forms a 1 cm string when lifted from the glass slab with a cement spatula. A reamer coated with the mixed Endoflas will be used to insert the material into the prepared root canals and pressure applied with a sterile cotton pellet to ensure optimal canal obturation.Access cavity will be restored with a bulk-fill high-strength glass ionomer cement (3M ESPE Ketac Molar, Seefeld, Germany). Post-operative radiograph will be taken to confirm fidelity to the pulpectomy procedure.The pulpectomy-treated tooth will be prepared for receiving a full coverage SSC one week after the pulpectomy.

Post-operative instructions for both pulpotomy and pulpectomy treatment groups will advise patients to take analgesics if necessary and to return if the pain is intolerable.

### Follow-up timeline

Children enrolled in the study will be followed from the trial intervention until the end of the study (two years post-treatment). Trial participants and their parents/guardians will be initially contacted by phone 24 h after the treatment intervention to record their post-operative pain intensity score using the VAS. Post-operative pain intensity score will also be recorded 7 d after the treatment intervention before the placement of the SSC. Clinical and radiographic outcome data of the treated tooth will be recorded at 6 months, 12 months, and 24 months post-treatment. Children participating in the trial will be advised to continue their routine dental visits, with the recall period determined by their caries risk status. Any symptomatic visits to the dentist outside these follow-up timepoints will be identified and reason for the same recorded on the trial record form.

### Trial outcomes

#### Primary outcomes

Clinical outcomes will be assessed by a single experienced paediatric dentist who shall be blinded to the treatment allocation. Radiographic outcomes will be assessed independently by two experienced paediatric dentists under optimum viewing conditions.

*Clinical success* of the treated tooth will be determined if all the following conditions are met:Absence of pain or discomfortAbsence of tenderness on percussion and palpationAbsence of any associated parulis/fistulaAbsence of any associated soft tissue swellingAbsence of any associated pathological mobility

*Radiographic success* will be determined as follows:Absence of pathosis on recall periapical radiograph i.e., no signs of pathological internal/external root resorption or new furcal/periapical lesions.Complete radiographic healing or reduction/no change in size of the any pre-operative furcal rarefaction. Teeth that show an increase in the size of any pre-operative furcal radiolucency will be considered as failed.

#### Secondary outcomes

*Immediate post-treatment pain relief:* post-operative pain felt by the child in the immediate aftermath of the trial interventions will recorded at two time-points (24 h and 7 d) using the VAS. The pain scores recorded will be used to evaluate pain reduction afforded by the two trial interventions.

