**Methods/design:**

This clinical study is a parallel, two-armed, open label, non-inferiority RCT with a 1:1 allocation ratio between the experimental intervention arm (pulpotomy) and the active comparator arm (pulpectomy). Healthy cooperative children, between 4–9 years of age, who have painful primary molars with clinical symptoms typical of irreversible pulpitis will be recruited after obtaining informed consent from their parents/legal guardians. 50 vital primary molars clinically diagnosed with symptomatic irreversible pulpitis will be randomly distributed between the two treatment arms. The primary outcomes that will be assessed are clinical and radiographic success after six-months, one-year and two-years of the trial interventions. The influence of baseline pre-operative variables (age; gender; tooth type; site of caries; pre-operative furcal radiolucency; pre-operative pain intensity) and intra-operative factors (time taken to achieve haemostasis) on treatment outcomes will also be assessed. The secondary outcome evaluated will be the immediate (24 h and 7 d) post-operative pain relief afforded by the two treatment interventions.

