### Target sample size

Sample size determination for this binary outcome non-inferiority randomised trial was calculated using a computer-generated system available online (https://www.sealedenvelope.com/power/binary-noninferior/). Based on previous clinical studies [29–31], a 95% success rate was assumed for both treatment interventions along with a 17% non-inferiority margin. Even an overall success rate of 78% for the experimental pulpotomy intervention would be considered non-inferior to the standard pulpectomy intervention. To obtain a power of 80% (β = 0.20) and a 2-sided α equal to 0.05, approximately 42 patients for both groups will be needed. To compensate for loss during follow-up and other causes of attrition, the targeted sample size will be 50 vital primary molar teeth diagnosed with irreversible pulpitis, distributed equally between the two trial treatment arms.

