### Statistical methods

All analyses will use the ‘intention to treat’ principle. Baseline demographic and clinical data will be summarised for each treatment group. Binary logistic regression models will be applied to analyse all outcome measures stated in the protocol adjusting for covariates thought to be of prognostic importance. Appropriate parametric or non-parametric tests will be used to determine any significant relationship between treatment outcomes and variables in the study (age, gender, tooth/caries type, and pre-operative furcal rarefaction/pain intensity). For all statistical tests, we will use 2-sided *p*-values with α ≤ 0.05 and the treatment effect estimates will be presented with 95% confidence intervals. Up-to-date versions of SPSS (Chicago, IL, USA) will be used to conduct the statistical analysis.

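### The only secondary outcome is worded as pain reduction, and the analysis does not secure adjustment for the pre-operative score; comparing the 24 h and 7 d scores adjusted for it would be a free gain in precision

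*Protocol article*

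**What the plan says.** The Secondary outcomes section has one entry, pain soon after treatment, which "will recorded at two time-points (24 h and 7 d) using the VAS". It then gives the use of these scores: "The pain scores recorded will be used to evaluate pain reduction afforded by the two trial interventions". The abstract calls the same outcome pain relief: "The secondary outcome evaluated will be the immediate (24 h and 7 d) post-operative pain relief afforded by the two treatment interventions".

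A baseline on the same scale exists. Under Trial interventions, "Pre-operative pain intensity will be recorded using the validated five-face visual analogue scale (VAS"), and the first seven steps, which include this one, apply to both arms. Each child should therefore have three face scores: pre-operative, 24 h and 7 d.

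On analysis, the Statistical methods section says: "Binary logistic regression models will be applied to analyse all outcome measures stated in the protocol adjusting for covariates thought to be of prognostic importance". Pre-operative pain appears there only in the next sentence, which plans tests of relationship between treatment outcomes and "variables in the study (age, gender, tooth/caries type, and pre-operative furcal rarefaction/pain intensity"). The Objectives likewise list it as a baseline variable whose influence on outcome will be studied.

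On size, "the targeted sample size will be 50 vital primary molar teeth diagnosed with irreversible pulpitis, distributed equally between the two trial treatment arms", which is 25 teeth per arm.

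**The concern.** A reduction needs a reference value, and among the three recorded scores the pre-operative one is the natural choice. Subtracting it carries its variability into the outcome. Where pain at presentation is only loosely related to pain after treatment, that variability is mostly noise in the between-arm comparison. A child who starts low on a five-face scale also has little room to show a reduction.

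Using the pre-operative score as a covariate removes only the part of the post-operative score that it predicts. In large samples this is never less precise than an unadjusted change.

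The analysis section does not settle which of the two is done. Its covariates are unspecified ("adjusting for covariates thought to be of prognostic importance"). The one adjusted model it names needs a yes/no outcome, while a five-face score or its reduction is not binary and no cut-point is given.

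The sample size was set for the binary success outcome alone, so nothing in the plan protects the precision of the pain comparison.

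**Working it through.** **The plan's own figures.** No SD, correlation, power or sample size is given for pain, so there is no plan figure to reproduce. The stated total of 42 belongs to the binary primary outcome and does not bear on this point.

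**Inputs.** From the document: 25 teeth per arm (50 split equally), two-sided level 0.05, a pre-operative score on the same scale. Assumed, because the document gives neither: the correlation rho between pre- and post-operative scores, and k = SD post / SD pre.

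**Formulas, equal SDs (k = 1), in units of SD²**
- Unadjusted reduction: variance 2(1 − rho)
- Post-operative score adjusted for baseline: variance 1 − rho²
- Ratio: 2(1 − rho)/(1 − rho²) = 2/(1 + rho)
- Equivalent number per arm: 25 × (1 + rho)/2
- Detectable difference at 80% power: (1.96 + 0.84) × √(2 × variance/25)

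| rho (assumed) | Variance, reduction | Variance, adjusted | Ratio | Equivalent n of 25 | Detectable difference in SD, reduction vs adjusted |
|---|---|---|---|---|---|
| 0.2 | 1.60 | 0.96 | 1.67 | 15.0 | 1.00 vs 0.78 |
| 0.5 | 1.00 | 0.75 | 1.33 | 18.8 | 0.79 vs 0.69 |
| 0.8 | 0.40 | 0.36 | 1.11 | 22.5 | 0.50 vs 0.48 |

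The shares of the sample lost are 1 − 15/25 = 40%, 1 − 18.75/25 = 25% and 1 − 22.5/25 = 10%. Estimating one extra coefficient costs little: inflating the adjusted variance by 1 + 1/46 moves the adjusted/reduction ratio at rho 0.5 from 0.75 to about 0.77.

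**Unequal SDs.** The adjusted variance as a share of the reduction variance is k²(1 − rho²)/(1 + k² − 2·rho·k). For rho from 0.2 to 0.7:
- k = 0.5: 0.23 to 0.25
- k = 0.75: 0.43 to 0.56
- k = 1: 0.60 to 0.85
- k = 1.25: 0.73 to 0.98

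The loss therefore grows when post-operative scores are less spread than pre-operative ones, and shrinks when they are more spread.

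**When the loss is nil.** Write Y0 for the pre-operative score, Y1 for the post-operative score and D = Y0 − Y1. If Y1 = a + b·arm + c·Y0 + e, then D = −a − b·arm + (1 − c)·Y0 − e. Apart from sign, the arm effect and its standard error are identical. In a linear model that includes the pre-operative score, it does not matter whether reduction or the post-operative score is analysed.

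**The case against.** The strongest reply is that the protocol never plans an unadjusted change-score test. It does not write pre-operative minus post-operative, it promises covariate adjustment for all outcome measures, and it lists pre-operative pain among the study variables. With that score as a covariate in a linear model the loss is zero, as shown above. The exact covariate and summary measure for a secondary outcome are also commonly left to an analysis plan, which is not shown here.

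Much of this stands. A reader might infer that an unadjusted comparison of reductions is the planned analysis, but the text does not say so, and the loss above is conditional on it. The point is not that detail is missing. The article itself names the quantity as reduction and fixes a model that cannot take it without a cut-point. It mentions pre-operative pain only for tests of relationship, so its promise of adjustment does not reach the pain score in usable form.

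Three stronger readings are not supported:
- **Power is roughly halved.** Under equal spread, with an assumed difference of 0.8 SD and rho 0.5, power is 81% for the reduction against 90% for the adjusted score. A gap near half needs post-operative scores bunched at the no-pain end. That is possible, but the document gives no figure for it.
- **The wording credits each procedure with the whole fall in pain within its arm.** The sentence concerns two randomised interventions, and no within-arm test is planned.
- **A real benefit is likely to be missed.** The Discussion voices only a general hope of less pain and discomfort, not tied to these scores, and no expected difference is stated.

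**Conclusion.** The point holds as a free improvement, not as an error that invalidates the comparison. The outcome is worded as a reduction, and the only named model does not fit a five-face score. Nothing in the article ensures that the pre-operative score enters the pain comparison.

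If reduction were compared without adjustment, the cost with equal SDs would equal about 40%, 25% or 10% of the sample at rho 0.2, 0.5 or 0.8. It could exceed that if post-operative scores are the less spread, and it is zero if baseline is already a covariate in a linear model. All of these figures rest on assumed correlations and SDs. At high correlation with equal SDs the gain is modest.

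**What to change.** In Secondary outcomes, replace the sentence on the use of the pain scores with: *The comparison is the between-arm difference in the 24 h face score, and in the 7 d face score, each with its 95% confidence interval; reduction from the pre-operative score is shown descriptively.*

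In Statistical methods, add: *The 24 h and 7 d face scores are analysed with a linear or ordinal model with the pre-operative face score as covariate, in place of binary logistic regression for this outcome.* The choice between linear and ordinal should be made before the data are seen.

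The cost is one sentence in each section. No new data, visits or participants are needed, because the pre-operative score is already collected in both arms.

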### Target sample size

Sample size determination for this binary outcome non-inferiority randomised trial was calculated using a computer-generated system available online (https://www.sealedenvelope.com/power/binary-noninferior/). Based on previous clinical studies [29–31], a 95% success rate was assumed for both treatment interventions along with a 17% non-inferiority margin. Even an overall success rate of 78% for the experimental pulpotomy intervention would be considered non-inferior to the standard pulpectomy intervention. To obtain a power of 80% (β = 0.20) and a 2-sided α equal to 0.05, approximately 42 patients for both groups will be needed. To compensate for loss during follow-up and other causes of attrition, the targeted sample size will be 50 vital primary molar teeth diagnosed with irreversible pulpitis, distributed equally between the two trial treatment arms.

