**Discussion:**

This trial seeks to provide evidence on whether pulpotomy treatment can be no worse than the standard pulpectomy treatment for the management of symptomatic irreversible pulpitis in vital primary molars.

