There are several advantages if pulpotomy can be offered as a substitute to the standard pulpectomy treatment for the management of irreversible pulpitis in vital primary molars. The ribbon-like torturous root canal anatomy in primary molars makes pulpectomy a difficult procedure for general dentists to perform, often requiring a child in pain to be referred to a specialist paediatric dentist for definitive treatment. In many situations, specialist care may not be easily accessible, or parents may not be able to afford its costs. Consequently, some parents may opt to extract the painful primary molar tooth of their child, resulting in complications such as the loss of function and arch integrity. The technically simpler pulpotomy procedure is not only less challenging for general dentists but is also potentially less time-consuming and easier for young patients to tolerate, both very important advantages in the dental treatment of children. Moreover, the pulpotomized primary tooth retains the regenerative/repair potential of the remnant radicular pulp and the proprioceptive sensation of the tooth. Finally, treatment complications sometimes associated with pulpectomy (e.g., extrusion of root filling material beyond the primary root apex) can be avoided if pulpotomy is the treatment of choice.

There is limited research on whether pulpotomy can be offered as an alternate treatment to pulpectomy in vital primary molars diagnosed with irreversible pulpitis. A prospective cohort study of pulpotomy in 50 vital primary teeth with irreversible pulpitis reported 93% clinical success and 90% radiographic success after one year of treatment [29]. A more recent retrospective study found higher clinical success rates for pulpotomy (99%) than pulpectomy (88%) in primary molars with carious pulp exposures or symptomatic irreversible pulpitis over an 18-month period [30]. To the best of our knowledge, there have been no RCTs comparing treatment outcomes of pulpotomy vs. pulpectomy for management of irreversible pulpitis in vital primary molars. This study aims to fill this research gap and could be of great importance in initiating a paradigm shift in the treatment of vital primary molars diagnosed with irreversible pulpitis. The objectives and hypothesis of the study are detailed below.

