## Discussion

The proposed study is unique in that for the first time a non-inferiority RCT is evaluating whether the experimental pulpotomy treatment can prove to be no worse than the standard pulpectomy treatment for the management of symptomatic irreversible pulpitis in vital primary molars. Considering that pulpotomy has been shown to have highly successful treatment outcomes in vital mature permanent molars diagnosed with irreversible pulpitis, there exists the possibility of similar successful outcomes in primary molars too. Consequently, this trial has the potential to produce new knowledge and add information to an area that is currently under researched.

It is important to highlight that the root filling material proposed to be used in the pulpectomy intervention group (Endoflas) has among the highest success rates reported for primary root canal filling materials [31–35]. Similarly, the new generation MTA product proposed to be used in the pulpotomy intervention group not only retains the biocompatibility, immunomodulatory, osteogenic, and sealing properties of traditional MTA, but being a resin-free pre-mixed bioceramic has superior handling characteristics, faster washout and setting times [36, 37]. The NaOCl proposed to be used as the haemostatic/disinfection agent in the pulpotomy intervention group demonstrated comparable clinical/radiographic success to traditional pulpotomy medicaments like formocresol and ferric sulphate without their drawbacks [38–40]. The two-year follow-up period proposed in this study should be adequate to assess treatment success of the trial interventions in primary molar teeth. Studies with longer follow-up periods can be planned based on the initial results of this study.

If the hypothesis of the proposed study is confirmed, it will support the clinical application of more conservative treatment approaches to vital primary teeth with irreversible pulpitis. Such an approach has the potential to cause less pain and discomfort to paediatric patients, have a shorter chair-time, and lower the technical difficulty and cost of managing complicated pulp conditions in vital primary molars.

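### The planned conclusion says less than the 17-point margin allows: a pass would show pulpotomy is under 17 points worse, and the analysis is not planned on that scale

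*Protocol article*

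**What the plan says.** The Target sample size section of the protocol article fixes the margin: "a 95% success rate was assumed for both treatment interventions along with a 17% non-inferiority margin". It spells out the consequence: "Even an overall success rate of 78% for the experimental pulpotomy intervention would be considered non-inferior" to pulpectomy. The same sentence that sets the rate and the margin points to three earlier clinical studies. The section gives no reason why a loss of 17 points is acceptable. The error level is given as "2-sided α equal to 0.05".

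The sections that word the trial's answer do not carry the margin. The abstract's Discussion says the trial asks "whether pulpotomy treatment can be no worse than the standard pulpectomy treatment". The main Discussion says it evaluates "whether the experimental pulpotomy treatment can prove to be no worse than the standard pulpectomy treatment", and adds that confirmation would support using more conservative treatment in practice.

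The Statistical methods section plans binary logistic regression with covariate adjustment for all outcomes, two-sided p-values, and effect estimates with 95% confidence intervals. It names neither a risk difference nor a comparison of a confidence limit with the margin.

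**The concern.** A non-inferiority result means only what its margin means. Here the margin is an absolute 17 points on a treatment assumed to fail in 5% of teeth, so the tolerated region is wide relative to the failure rate. A conclusion worded as no worse than the standard, with the 17 points left out, claims more than a pass can show.

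The planned analysis adds to this. Logistic regression yields an odds ratio, and a two-sided p-value for a difference does not test the margin. A reader of the results could be told that pulpotomy is no worse without seeing the one interval that bears on the claim. At stake is how strongly the result can be set against pulpectomy, which the Background describes as the guideline recommendation.

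**Working it through.** **Inputs.** From Target sample size: 95% success in both arms, 17-point margin, 80% power, two-sided 0.05, about 42 evaluable, 50 enrolled. With 1:1 allocation that is 21 to 25 teeth per arm.

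**The plan's own figure.** With unpooled variance and equal rates, n per arm = (z₁₋α + z₀.₈)² × 2 × 0.95 × 0.05 / 0.17².
- One-sided 0.05: 20.3, so 21 per arm and 42 in total. This matches the article.
- One-sided 0.025, the equivalent of the stated two-sided 0.05: 25.8, so 26 per arm and 52 in total.

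The stated 42 therefore fits one-sided 0.05. That mismatch is a separate matter. The figures below use 95% limits because that is the level the article states for its intervals.

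**What the margin tolerates.** 95 − 17 = 78% success, so failure of 22% against 5%. The ratio is 22/5 = 4.4, and the excess is 17 per 100, or about one extra failed tooth in every six treated (1/0.17 ≈ 5.9).

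**What a pass would exclude.** All pairs of binomial outcomes were enumerated with pulpectomy at a true 95%. A pair passes if the lower 95% limit for pulpotomy minus pulpectomy lies above −17 points. Chance of passing, 21 / 25 teeth per arm:

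| True pulpotomy success | Wald 95% | Newcombe 95% |
|---|---|---|
| 95% (equal) | 73.4% / 72.8% | 46.4% / 57.4% |
| 92.5% (failures 1.5-fold) | 54.9% / 53.8% | 31.2% / 39.3% |
| 90% (failures doubled) | 39.0% / 37.4% | 20.6% / 25.8% |
| 78% (at the margin) | 4.6% / 3.7% | 2.3% / 2.2% |

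**Observed results that pass.** The limit must clear −17 points, so the observed gap must be small. With 25 per arm and 24 pulpectomy successes, Wald 95%:
- 24 pulpotomy successes: 0 − 1.96 × √(2 × 0.96 × 0.04/25) = −10.9 points. Passes.
- 23 pulpotomy successes: −4 − 13.1 = −17.1 points, where 13.1 = 100 × 1.96 × √(0.92 × 0.08/25 + 0.96 × 0.04/25). Fails.

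**Scale of the analysis.** A 17-point loss is not one odds ratio. For 78% v 95% the odds ratio of success is (0.78/0.22)/(0.95/0.05) = 0.19. If pulpectomy succeeded in 88%, the figure the Background cites from a retrospective study, the margin would fall at 71% and the odds ratio would be (0.71/0.29)/(0.88/0.12) = 0.33. An odds ratio with its interval therefore cannot be read against −17 points without a further step, which the article does not describe.

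**The case against.** The article discloses the 78% openly, and no-worse wording is common shorthand in a declared non-inferiority trial. Both sentences describe the question asked, not a result. This stands in part: nothing is hidden. But the sections that readers will take the answer from do not carry the margin.

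The citation of earlier studies may be meant to cover the margin as well as the 95%, and a condensed article may leave the rationale to the full protocol. This stands. The missing rationale alone would be a request for detail. The Background also lists benefits that could be traded against efficacy, such as a simpler and possibly quicker procedure, though it does not link them to 17 points.

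The article already promises effect estimates with 95% confidence intervals. That stands too, but the only model it names gives odds ratios.

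Two stronger readings are tempting, and the document does not support them.
- A reader might infer that 22% observed failure would be declared non-inferior, and the article's sentence about 78% invites that. It would not be: passing depends on the confidence limit, and a true 78% passes only about 2–5% of the time with 95% limits.
- A reader might set the margin against the 11-point gap in the Background (99% v 88%) and call 11 points the protocol's own threshold. That gap comes from one retrospective study with a mixed indication, favours pulpotomy, and is nowhere called a tolerable or important loss. Requiring 11 points to be excluded would also often block a truly equivalent treatment: with 25 per arm and equal 95% rates, power at an 11-point margin is about 43% at one-sided 0.025.

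**Conclusion.** The concern holds as a mismatch between claim, margin and analysis. A pass would establish that pulpotomy is less than 17 points worse in success, which on the article's assumption leaves room for failure of up to 22% against 5%. It would not rule out a smaller but real increase: a true doubling of failures passes in 37–39% of trials with Wald limits and 21–26% with Newcombe limits.

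These figures assume pulpectomy success of 95%, independent teeth, 21 to 25 evaluable teeth per arm, an unadjusted comparison and 95% limits. They do not show that the margin is wrong or that a pass would be worthless. They show that the conclusion needs the margin in it and that the verdict needs an estimate on the margin's scale. This is a cheap improvement to the plan and does not call for a redesign.

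**What to change.** Keep the sample size and the margin.

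1. In Statistical methods, pre-specify that non-inferiority is judged on the risk difference in success (pulpotomy minus pulpectomy) with its 95% confidence interval, the lower limit being compared with −17 points. Name the interval method, since Wald and Newcombe limits differ noticeably at this size. Report the interval beside the verdict. The logistic models can stay for the covariate questions.
2. In the abstract's Discussion and the main Discussion, word the conclusion as *not more than 17 percentage points worse in success rate*, and say that this allows failure of up to 22% against an assumed 5%.
3. As supporting detail, give the reason for the 17 points in Target sample size.

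The cost is a change of wording and one reported interval, with no extra children or visits. The downside is a less favourable headline claim.
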